#### FEASIBILITY:

In this multicenter randomized trial, performed by the Orthopaedic Consortium Mid-West Netherlands, nine centers participate with large volumes of meniscectomies (over 4000 meniscectomies annually). The Onze Lieve Vrouwe Gasthuis Amsterdam, Academic Medical Center Amsterdam, Diaconessenhuis Utrecht, the Sint Lucas Andreas Ziekenhuis Amsterdam, the Medisch centrum Jan van Goyen, the Medisch Centrum Alkmaar, the Sint Elisabeth Ziekenhuis Tilburg, the Slotervaart Ziekenhuis Amsterdam, Medisch centrum Haaglanden and the Tergooi ziekenhuis Hilversum. Despite age criteria and exclusion of mechanical obstruction, we expect a high recruitment rate, since patients will not be refrained from surgery in the long run. Assuming a participation of 30-40%, we therefore expect that inclusion will be completed within 27 months and all patients have finished their follow-up no later than 48 months after the start of the study.

## 7. TREATMENT OF SUBJECTS

### Intervention group:

Arthroscopic partial APM is performed within 4 weeks in day-care by an (orthopaedic) surgeon experienced in arthroscopic surgery, or by a resident skilled in arthroscopic knee surgery under direct supervision of an orthopaedic surgeon experienced in arthroscopic surgery. Eight weeks after surgery (3 months after randomization), patients will visit the outpatient department to check for function and persistence of symptoms. Since standard PT after APM has not been proven effective, patients will only be referred to a physical therapist in case of swelling or signs of atrophy, as advised by the Dutch Orthopaedic Association Guidelines (1).

### Control group:

PT consists of 2 sessions of 30 minutes per week for 8 weeks, with a total of 16 sessions. Patients will also be given a home exercise program (appendix B). These programs are based on a physical therapy program used by Herrlin et al. (6) and is adjusted for our population by a physical therapist (dr. [name]; member of the research group) who earned his PhD degree in the field of the anterior cruciate ligament and is specialized on the knee. After completion of the PT-sessions, patients will visit the outpatient department to check for function and persistence of symptoms.

### Delayed surgery group:

Based on patients complaints, findings during physical examination and the level of pain, the physician and/or surgeon and patient will decide in agreement that conservative treatment has failed and choose for delayed arthroscopic partial meniscectomy. This can be done no earlier than 3 months after randomization during the entire follow up time of the study. Prior to the delayed APM patients will be asked to answer an extra questionnaire as endpoint of PT. Patients in this group will be analyzed in the PT group according to the Intention-to-treat principle.

#### 7.1 Use of co-intervention (if applicable)

Medicational use, in terms of analgetics are allowed to use during the study duration.

Patients will be asked for the use of analgetics during the study.

#### 7.2 Escape medication (if applicable)

Not applicable.

## 8. METHODS

### 8.1 Primary and secondary outcome measures

#### 8.1.1 Primary outcome

Primary outcome will be change in physical function from baseline to 2 years measured by the International Knee Documentation Committee (IKDC) 'Subjective Knee Form', which has been validated for meniscal injuries (18). The IKDC is developed for knee-specific measurement of symptoms, function, and sports activities in patients with ligament and meniscal injuries. The IKDC is a self-administered questionnaire with a total of 19 questions. All items, except item 10a, are converted to a score with a maximum of 100 indicating no restrictions in daily and sports activities and the absence of symptoms. A difference of more than 8.8 points in IKDC-score is deemed clinically relevant.

In addition, we will perform an economic analysis alongside the RCT from a societal perspective and a budget impact analysis from societal, government and insurer perspective.

#### 8.1.2 Secondary Outcomes

1) Change in:

- General health, measured by RAND-36
- Quality of life, measured by EQ-5D5L
- Pain, measured with the VAS in rest and during weight bearing.
- Level of activity, measured by Tegner Activity Scale (TAS)
- Patient specific complaints measured by the PSC (patient specific complaints) Questionnaire
- Treatment group; number of patients initially treated conservatively, treated secondarily by APM.

We will use the EQ-5D5L to measure Quality Adjusted Life Years (QALY).

2) Productivity losses and the use of healthcare services, measured by a modified version of the Trimbos/iMTA questionnaire for Costs associated with Psychiatric Illness (TiC-P).

3) Relation between a participants expectation of treatment and their satisfaction.

4) PE, consisting of performance on physical tests (squatting with duckwalk, Thessaly test, McMurray), the range of motion, joint line tenderness and the existence of joint effusion in the knee.

5) Adverse events including:

- Minor: prolonged synovial fluid leakage from arthroscopy portals and bleeding.
- Moderate: surgical site infection, vascular and neurological damage
- Severe: septic arthritis, cardiac events, pulmonary embolism and death.

Surgical instrument malfunction will be recorded, as well as reoperations including knee arthroplasties and re-hospitalization.

6) We plan a follow up moment at 60 months to see the progression of osteoarthritis, measured with the Kellgren Lawrence Grading Scale for Osteoarthritis.

Hypotheses:

1) We assume equal improvement of physical function in both groups (a difference of < 8.8 points on IKDC 'Subjective Knee Form'). This would question the role of arthroscopic surgery in treatment of symptomatic, non-obstructive meniscal injuries in patients over 45 years old.

2) We assume with an equal improvement of function in both groups, that an initial conservative approach for this condition in older patients is much more cost-effective than APM as standard therapy.

3) We assume a lower baseline value of participants compared to the average score of the Dutch population and an equal improvement of general health in both groups (RAND-36).

4) We assume equal improvement of quality in life, measured in QALY's.

5) We assume equal improvement of pain, measured with the VAS score.

6) We assume equal improvement of activity level (Tegner Activity Score).

7) We assume equal improvement of complaints in activities and movements found most important by patients (patient specific complaints).

8) We expect a greater reduction of joint line tenderness in the arthroscopic partial meniscectomy group shortly after therapy, compared to the physical therapy group, since part of the damaged meniscus is released. However, we expect no difference in joint line tenderness on the long term. We expect a faster reduction of joint effusion after treatment in the physical therapy group. However, we do not expect a difference between both groups after 24 months. We do not expect a significant improvement of ROM after treatment in both groups.

9) We estimate that 2/3 of surgeries can be prevented (as stated by Herrlin SV et al. (6), and therefore expect 1/3 of patients who will undergo delayed arthroscopic meniscectomy after completion of physical therapy. The possible cost reduction of this effect will be calculated in the economic analysis.

10) Patients in the physical therapy group will leave work for at least 16 sessions of 30 minutes each week, representing one working day, with the addition of travelling time. Patient in the surgery group are expected to be absent from work for one working day, the day of surgery. We therefore expect surgery to lead to more productivity losses.

11) We expect squatting to have the greatest predictive value of the different meniscal tests for detecting meniscal injuries.

12) We expect a faster development or progression of osteoarthritis after arthroscopic partial meniscectomy compared to physical therapy.

13) We expect adverse events to occur more frequently in the arthroscopic partial meniscectomy group. Patients who are subjected to delayed surgery after physical therapy has failed, remain in the physical therapy group. Therefore, we do expect adverse events to occur in the physical therapy group. Since the number in the arthroscopic partial meniscectomy group are to be expected to outnumber the number of patients with delayed surgery, we expect more adverse events in the arthroscopic partial meniscectomy group.

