#### **4. OBJECTIVES**

The objective of this study is to evaluate the effectiveness and cost-effectiveness of surgical and conservative treatment of non-obstructive meniscal injuries in older patients

Hypothesis:

We assume equal improvement of physical function in both groups and reduced costs with conservative treatment.

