#### 6.4 Sample size calculation

Sample size is based on a power of 90%, an alpha of 0.05, a standard deviation of 18 points and a non-inferiority threshold of 8 points on the IKDC (a minimal clinical important change in IKDC is 8.8) (18).

We calculated that with 10% loss to follow-up after 24 months and 25% delayed APM in the PT group, 160 patients are needed per group in this non-inferiority RCT.

This corresponds to a total of 320 patients will be included.

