## 10. STATISTICAL ANALYSIS

Data-analysis and presentation:

To investigate the effect of surgery, we will use generalized estimating equations (GEE) for longitudinal analysis in SPSS 18 on an intention-to-treat and per-protocol basis, as well as sub-group analysis of the cross-over patients. This method takes into account the dependency of observations within a patient, and the fact that not all patients may be assessed at each time point (missing data). In the primary GEE model, the outcome variable studied (e.g. physical function on the IKDC) will be analyzed as a dependent variable, using treatment allocation (1, intervention; 0, control) and time as a key independent variables. In the secondary GEE model, the outcome variables studied (e.g. general health on the RAND36, quality of life on the EQ5D-5L, level of activity on the TAS, knee pain on the question 10 of IKDC, the correlation between a patient's expectation and satisfaction, productivity losses on TiC-P, muscle strength, range of motion, squatting and adverse events) will be analyzed in a similar way. To evaluate whether the two groups differed in change over time the interaction term of group and time (group X time) will be assessed. Time will be included as a dummy variable (reference = baseline T0), and four interaction terms will be analyzed (T1Xgroup; T2x group; T3x group, T4x group). All models will be corrected for center of inclusion and age group. In additional analysis, we will investigate the possible confounding effect (defined as more than 10% change in the parameter estimate for groupXtime) of 5 variables (body mass index, gender, profession, ASA-classification, the affected meniscus, the type of tear and the stadium of OA according to the Kellgren Lawrence Grading Scale for Osteoarthritis).

At the following time points following the treatment (T2, T3, T5 and T7) we will describe the incidence of revisions (intervention group) or treatment failures (=delayed APM, control group) using descriptives. After two years (T7) we will compare the incidence of development or progression of OA between groups using a chi-squared test (or Fisher's Exact as appropriate). For all analysis, a two-tailed value of  $p < 0.05$  is considered to be significant.

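### ITT non-inferiority would support PT first with optional delayed APM, not conservative treatment alone as the objective and Hypothesis 1 are worded

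*Protocol*

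**What the plan says.** Section 4 sets out to "evaluate the effectiveness and cost-effectiveness of surgical and conservative treatment of non-obstructive meniscal injuries in older patients". The Summary (Section 2) likewise describes a comparison of surgical with conservative treatment and says that two groups of 160 are needed to prove non-inferiority of conservative therapy. Hypothesis 1 in Section 8.1.2 assumes equal improvement and concludes: "This would question the role of arthroscopic surgery in treatment of symptomatic, non-obstructive meniscal injuries in patients over 45 years old".

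Section 7 (Delayed surgery group) allows PT patients to have APM from 3 months after randomization until the end of follow-up, and analyses them in the PT group under ITT. It adds: "Prior to the delayed APM patients will be asked to answer an extra questionnaire as endpoint of PT". The expected share is 25% in Sections 5 and 6.4. Hypothesis 9 gives a different figure: "therefore expect 1/3 of patients who will undergo delayed arthroscopic meniscectomy after completion of physical therapy". Section 5 states that the trial is sized for ITT.

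Section 10 plans ITT and per-protocol analyses and a subgroup analysis of cross-over patients. It then anticipates, within ITT, a 25% dropout that is non-ignorable and related to the intervention, to be handled by weighted GEE.

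**The concern.** The objective and Hypothesis 1 speak of conservative treatment, but the PT arm as analysed includes the 24-month results of patients who also had surgery. If delayed APM helps those in whom PT failed, that gain counts for PT and moves the ITT difference towards zero. In a non-inferiority trial this favours the claim. PT without surgery could then fall short of APM by more than the margin, and possibly by more than the protocol's own clinically relevant difference, while the ITT result is still declared non-inferior. Section 12.5 intends the results for reimbursement decisions and guidelines, and one budget-impact scenario has all patients receiving PT, so the exact scope of the conclusion matters.

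**Working it through.** **Inputs.**
- Section 6.4: "a power of 90%, an alpha of 0.05, a standard deviation of 18 points" and "a non-inferiority threshold of 8 points on the IKDC"; also "a minimal clinical important change in IKDC is 8.8".
- Sections 5 and 6.4: 10% loss to follow-up and delayed APM share c = 25%. Hypothesis 9: c = 1/3.
- Sidedness is not given with the sample size. Section 10 says "For all analysis, a two-tailed value of" p < 0.05, which is one-sided 0.025 for non-inferiority.
- Not in the protocol: the share b of the APM advantage that a delayed-APM patient has gained by month 24. It is varied below.

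**Step 1: reproduce 160 per group.** n = 2 × [18 × (1.960 + 1.282) / 8]² = 106.4, so 107. Then 107 / (0.90 × 0.75) = 158.5, so 159, against 160 stated. Adding the two rates to 35% gives 106.4 / 0.65 = 163.7, so 164, also close. At one-sided 0.05 the base is 87, and 87 / 0.675 = 128.9, so 129, which does not match. Inflating for dilution instead of loss gives 106.4 / (0.90 × 0.75²) = 210.2, so 211, which does not match either. The stated figure is thus consistent with one-sided 0.025 and with counting delayed-APM patients as lost, although Section 7 keeps them in the analysis.

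**Step 2: what the ITT margin means for PT alone.** Let d be the true advantage of APM over PT alone. If a share c of the PT arm gains b × d from delayed APM, the ITT difference is d × (1 − c × b). An ITT difference of 8 then corresponds to d = 8 / (1 − c × b).

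| Benefit b | d at c = 25% | d at c = 1/3 |
|---|---|---|
| 0 | 8.0 | 8.0 |
| 0.5 | 8 / 0.875 = 9.1 | 8 / 0.833 = 9.6 |
| 1 | 8 / 0.75 = 10.7 | 8 / 0.667 = 12.0 |

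The deficit passes 8.8 when c × b = 1 − 8 / 8.8 = 0.091, that is b = 0.36 at c = 25% or b = 0.27 at c = 1/3.

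**Step 3: chance of declaring ITT non-inferiority when PT alone is 8 points worse.** With 160 × 0.90 = 144 per arm, SE = 18 × √(2 / 144) = 2.12. The probability is Φ[(8 − ITT difference) / 2.12 − 1.96].

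| Benefit b | c = 25% | c = 1/3 |
|---|---|---|
| 0 | difference 8.0: 2.5% | difference 8.0: 2.5% |
| 0.5 | difference 7.0: 7% | difference 6.67: 9% |
| 1 | difference 6.0: 15% | difference 5.33: 24% |

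**Step 4: do the other planned analyses recover PT alone?** The per-protocol set would leave out patients who switched because PT failed. It therefore keeps the PT patients who did well and is optimistic for PT. The cross-over subgroup is defined after randomization, and Section 10 names no comparison for it. Neither estimates PT without surgery in the randomized population.

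**The case against.** The protocol often speaks of a strategy. Hypothesis 2 compares an initial conservative approach with APM as standard therapy. Section 3 and Hypothesis 9 rest the benefit on preventing two thirds of operations, not all. The Summary and Sections 11.1 and 11.3 present delayed surgery as part of the conservative arm. On that reading ITT is the right analysis, and non-inferiority would properly question surgery as the routine first step. This stands. A reader might infer that the trial cannot support its objective, or that the protocol means to conclude that APM has no role. The documents do not bear out either: the strategy question is legitimate, and to question a role is not to deny it.

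A reader might also take the probabilities in Step 3 as type I error inflation. They are not. The ITT test keeps its nominal error for the ITT hypothesis; the figures concern a different hypothesis, about PT alone.

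Full benefit is one end of the range. Delayed APM is allowed throughout follow-up, so late switchers have little time after surgery before month 24, and switchers are selected because PT failed. This also stands, so the range is reported and not its extreme.

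Finally, the analytic use of the questionnaire taken before delayed APM may be left to a statistical analysis plan that is not at hand. Its absence from Section 10 is not counted as a defect.

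What remains is that Section 4, the Summary and Hypothesis 1 do not carry the strategy wording found elsewhere.

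**Conclusion.** The point holds as a mismatch between the stated target and what the primary analysis estimates. ITT as described in Section 7 compares initial PT with optional delayed APM against immediate APM. Non-inferiority there does not by itself show that PT without surgery lies within 8 points of APM.

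The size cannot be fixed from the protocol. The margin tolerates a PT-alone deficit of 8 points if delayed APM adds nothing, 9.1 to 9.6 at half benefit and 10.7 to 12.0 at full benefit. When PT alone is 8 points worse, ITT non-inferiority is declared with probability 2.5%, 7 to 9%, or 15 to 24% respectively. These figures assume 144 evaluable patients per arm, SD 18, one-sided 0.025 and a common value of b among switchers.

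The target is also unsettled within the protocol. Section 7 retains delayed-APM patients in the PT arm. Section 10 applies the same 25% figure to non-ignorable dropout, and the sample size reproduces when they are counted as lost.

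**What to change.** 1. Reword the objective (Sections 2 and 4) and Hypothesis 1 as initial PT with optional delayed APM versus immediate APM, and limit the stated conclusion to routine immediate APM. This costs only wording and a narrower headline claim.
2. Reconcile Section 7 (delayed-APM patients kept in the PT arm) with the 25% dropout and weighted GEE in Section 10 and with the sample-size inflation. State one planning value for delayed APM in place of 25% and 1/3.
3. If the questionnaire before delayed APM contains the IKDC, which Section 7 does not say, use it in a supportive sensitivity analysis. Label this as pessimistic for PT and report it beside the per-protocol result, which is optimistic for PT. The cost is one analysis on data already collected.

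The analysis in item 3 should not be a condition for the claim. It replaces the 24-month endpoint with a score taken when PT was judged to have failed, possibly at month 3, and gives revisions in the APM arm no equivalent rule. With the arms otherwise equal, it would be expected to miss the margin once switchers' carried-forward scores fall short by more than (8 − 1.96 × 2.12) / c, that is 15.4 points at c = 25% or 11.5 points at c = 1/3.

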## 8.2 Randomization, blinding and treatment allocation

We will include 320 patients between 45 and 70 years with MRI-confirmed symptomatic, non-obstructive meniscal tears. Randomization will be performed in a 1:1 ratio by a computerized software program (TENALEA Clinical Trial Data Management System) using random blocks with maximum block size 6, stratified for center and age group.

- a. Open study (no blinding)
- b. Number of randomization arms : 2
- c. Specification of the arms : APM vs PT
- d. Weight of the arms : 1:1
  - Type of randomization : Random block, max block size 6
- e. Strata and categories:
  - Age : (45-57) and (57-70)
  - Centers : a maximum of 10
- f. No deletion or replacement of participants (unless false randomization due to clear technical issues)

At time of presentation at the outpatient department, people suspected for a meniscal injury will be informed about the study with an information letter. When they return to the outpatient department for the results of the MRI, they will be asked for participation in the study. After informed consent is signed, the local physician/surgeon contacts the randomization website and submits a patient's details and treatment center to the online TENALEA data management program and receives treatment allocation when submitting this information to the website. All data management will be recorded online, unless patients are unable or unwilling to complete the questionnaires online.

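### Section 8.2 discloses the maximum block size to the clinicians who recruit for an open, centre-and-age-stratified trial, so some assignments could be predicted before consent

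*Protocol*

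**What the plan says.** All the design facts are in the protocol, most of them in section 8.2.

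- **Blinding:** "Open study (no blinding".
- **Ratio:** "Randomization will be performed in a 1:1 ratio by a computerized software program".
- **Blocks:** "using random blocks with maximum block size 6, stratified for center and age group". The specification list repeats it: "Type of randomization : Random block, max block size 6". Neither place gives the individual sizes or their probabilities.
- **Strata:** "Centers : a maximum of 10", and two age groups.
- **Who randomises:** "After informed consent is signed, the local physician/surgeon contacts the randomization website", enters the patient and receives the allocation.
- **Who recruits:** section 11.2 has the treating physician or investigator introduce the study at the first visit and take consent at the MRI-result visit.

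Nothing in the protocol says that block details are kept from recruiting sites.

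**The concern.** Central web allocation hides the list, but it does not stop inference from the pattern of past assignments. Permuted blocks return to balance. In an open trial the earlier allocations at a site can be known, and a stated maximum tells the recruiting clinician how far the arms can drift apart before the next assignment is forced.

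The prediction would be available before consent, when the clinician decides whom to approach and how strongly to encourage participation. There is room for selection: the feasibility text after section 6.4 expects 30% to 40% of patients to take part. Section 3 also acknowledges that the result could mean fewer procedures for surgeons.

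If patients with a better or worse outlook were steered towards one arm, analysis by intention to treat would not repair it. The primary outcome is self-reported and the non-inferiority margin is 8 IKDC points. This point concerns what the protocol itself discloses, so a separate statistical analysis plan could not settle it.

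**Working it through.** The protocol gives no predictability figure to reproduce.

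**Inputs.** From the protocol: 1:1 ratio, maximum block size 6, up to 10 centres, 2 age groups, 320 patients. Balanced 1:1 blocks are even, so the possible sizes are 2, 4 and 6. Patients per stratum: 320 / (10 × 2) = 16, or 320 / (9 × 2) = 17.8 with the 9 clinics named in the summary. Assumed, because not stated: the mix of sizes. Also assumed: the clinician knows earlier allocations in the stratum.

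**Rule examined.** When the arms differ by 2 or more within the stratum, guess the arm that is behind.

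**Count per block.**
- Size 2: the difference never reaches 2 before an assignment.
- Size 4: 2 of the 6 arrangements start with two alike, so 2/6 = 1/3 of an assignment per block is made at a difference of 2. The next is always the lagging arm.
- Size 6:
  - Before position 3, the first two are alike with probability 2 × (3/6) × (2/5) = 0.4, and the lagging arm follows with probability 3/4, giving 0.3 correct.
  - Before position 4, the difference is 3 in 2 of 20 arrangements = 0.1, always correct.
  - Before position 5, the last two are alike with probability 0.4, always correct.
  - Total: 0.9 such assignments per block, of which 0.8 are guessed correctly.

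**Formulas**, with w2, w4, w6 the probabilities of each size and L = 2·w2 + 4·w4 + 6·w6:
- share at a difference of 2 or more = (w4/3 + 0.9·w6) / L
- accuracy there = (w4/3 + 0.8·w6) / (w4/3 + 0.9·w6)
- share at a difference of 3 = 0.1·w6 / L

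**Equal mix.** L = 4. Share = (0.1111 + 0.3) / 4 = 10.3%. Accuracy = (0.1111 + 0.2667) / 0.4111 = 91.9%. Share at a difference of 3 = 0.0333 / 4 = 0.8%.

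| Weights 2:4:6 | Share at ≥2 | Accuracy | Share at 3 |
|---|---|---|---|
| 1:1:1 | 10.3% | 91.9% | 0.8% |
| 1:2:1 | 9.8% | 93.6% | 0.6% |
| 6:2:2 | 7.7% | 91.9% | 0.6% |
| 0:1:1 | 12.3% | 91.9% | 1.0% |
| 0:3:1 | 10.6% | 94.7% | 0.6% |
| 0:1:3 | 13.8% | 90.1% | 1.4% |
| 1:0:1 | 11.3% | 88.9% | 1.3% |
| 1:1:8 | 14.0% | 89.4% | 1.5% |
| 0:0:1 | 15.0% | 88.9% | 1.7% |

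**Finite strata.** These are long-run values. Simulated strata of 16 with the equal mix give 9.4% to 9.7% at 91% to 92%. All blocks of size 6 give 14.3% at 86.7%. So the equal mix means 0.094 × 320 = 30 to 0.103 × 320 = 33 assignments. Over all mixes with maximum 6 the range is about 8% to 15% at 87% to 95%.

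**All assignments.** With the equal mix, guessing the lagging arm throughout and tossing a coin at balance is right about 70% of the time, against 50% by chance.

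**What the disclosure adds.** The lagging-arm rule does not use the maximum, so it works for anyone who keeps a count. Knowing the maximum tells the clinician that a difference of 3 forces the next assignment and that a difference of 2 is already near the limit.

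**The case against.** The case against is substantial, and much of it stands.

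- **The mix is assumed.** A reader might take accuracy above 90% as a property of the plan. It is not: several mixes with maximum 6 fall just below. Nor does the protocol say that blocks of 2 are used.
- **One surgeon doing everything.** A reader might infer that the same surgeon approaches, consents, randomises, operates and sees every allocation. Section 8.2 refers to the local physician or surgeon, section 11.2 to the treating physician or investigator, and section 7 allows a supervised resident to operate. Several recruiters who do not share allocations would lower predictability.
- **Pace.** Inclusion is planned over 27 months, about 117 weeks, so a stratum of 16 gains one patient roughly every 7 weeks (117 / 16 = 7.3). Keeping a count is possible but takes deliberate effort.
- **A bias in IKDC points.** A reader might want to convert predictability into points and compare it with the margin. The documents give no figure for how far steering would shift prognosis or how often it would occur. The primary outcome is change from baseline, so a difference in baseline level that simply persists is removed. Only selection on expected change would matter.
- **Larger blocks.** A reader might infer that the maximum of 6 is too small. In simulated strata of 16, sizes 6 to 12 lower overall guessing to about 64% and accuracy at a difference of 2 or more to about 77%. They also raise the share of assignments at such a difference to about 22%, and the SD of the within-stratum imbalance from 0.87 to about 1.36. That is a trade-off, not a correction.
- **Safeguards.** Allocation is central, released only after signed consent, and participants are not deleted or replaced. These protect the list and the period after allocation. They do not prevent a prediction made before consent.

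What remains is the disclosure itself. Nothing in the design requires recruiting sites to know the limit.

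**Conclusion.** The point holds as an avoidable disclosure. It rests on three assumptions: the block mix, a clinician who tracks earlier allocations within the stratum, and selection related to expected improvement in IKDC. On the first two, roughly a tenth of assignments could be predicted with about 90% accuracy, and about 1% with certainty because the maximum is known. The third decides whether any of this would affect the result, and the protocol neither shows nor excludes it. No size of bias in IKDC points can be supported from the documents. The point is a free improvement to the protocol text and does not invalidate the randomisation.

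**What to change.** In section 8.2, remove the maximum block size from both the opening paragraph and the specification list. Replace it with a statement that randomly varying permuted blocks are used, with sizes held by the data manager and not disclosed to recruiting sites. Keep the stratification by centre and age group.

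This costs one small protocol edit and no patients, and it needs no change to the randomisation system. It takes away the knowledge that a given assignment is forced. It does not prevent guessing the lagging arm from a running count. Whether to accept more within-stratum imbalance in return for lower predictability is for the trial statistician to decide separately, and this edit does not depend on that decision.
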